### Statistical analysis

Multivariate analysis with repeated measures will be conducted, using SPSS Statistics 19 to evaluate training effects on the primary and secondary outcomes.

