**Methods/design:**

The study consists of two parts: the first part is a randomised controlled trial with school-aged children (8–12 yrs) with AD(H)D. Two groups (each n = 50) will be randomly assigned to a well studied computerized working memory training ‘Cogmed’, or to the ‘Paying attention in class’ intervention which is an experimental school-based executive function training. Children will be selected from regular -and special education primary schools in the region of Amsterdam, the Netherlands. The second part of the study will determine which specific characteristics are related to non-response of the ‘Paying attention in class’ intervention. School-aged children (8–12 yrs) with AD(H)D will follow the experimental school-based executive function training ‘Paying attention in class’ (n = 175). Academic performance and neurocognitive functioning (primary outcomes) are assessed before, directly after and 6 months after training. Secondary outcome measures are: behaviour in class, behaviour problems and quality of life.

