### Randomisation

For the first study, the Clinical Research Unit of the Academic Medical Centre composed a randomisation list, stratified by age. Children will be individually randomised to either the Cogmed RM [10] or ‘Paying attention in class’ intervention group by a researcher independent of the research team. This researcher will subsequently inform the therapist about the allocated condition for each child. The PhD student and research assistant will be blind for the allocation.

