
### Measures and procedures

After written informed consent is obtained, parents will fill out an application package which contains questionnaires of demographic and background information such as previous care and medication use. The measurements of academic performance and neurocognitive functioning (primary outcomes) are administered in a child face-to-face meeting which takes place at three consecutive moments: at baseline, directly after treatment and 6 months after treatment. The test battery that will measure academic performance consists of an automated math [15], a spelling skill test [16] and technical literacy [17] test. The neurocognitive functioning test battery consists of tests that measure attention [18], verbal [19,20] and spatial working memory [21], inhibition [20], planning and goal-directed behaviour [22]. Also, both parents and teachers fill out the ‘The Behaviour Rating of Executive Functions’ [23] questionnaire. The secondary outcome measures of this study are behaviour in class, behaviour problems and quality of life of the children. This will also be measured at the three consecutive moments mentioned above. Behaviour in class will be reported by the teacher using the ‘Leervoorwaardentest’, a questionnaire [24]. Both teacher and parents will rate behaviour problems using ‘The Child Behavior Checklist for Ages 6–18 [25] and ‘Teacher’s Report Form for Ages 6-18’ [26]. Before training is started, the Diagnostic Interview Schedule for Children [27] and Social Communication Questionnaire [28] is administered to parents to rule out other behavioural problems or psychiatric problems that meet exclusion criteria. Finally, quality of life is measured by using the Kidscreen-27 [29] questionnaire and is completed by parents and the child. All tests and questionnaires have been selected based on results from a small pilot study and clinical experience. Most of the tests and questionnaires are in line with other relevant international literature. Other aspects that were taken into account were duration of administration, variety of neurocognitive tests that can establish possible near and far transfer effects and methodological points such as presence of Dutch norms and test-retest reliability. Table 1 gives an overview of all the assessments and outcome measures.

**Table 1 T1:** Outcomes measures

	**Measure**	**Informant**	T1	T2	T3

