	*I-DISC-IV (Diagnostic Interview Schedule for Children,* 27): structured diagnostic telephonic interview, registered via the internet. Measures presence of symptoms and criteria variables as defined by the DSM-IV [14]. Only the domains ADHD, ODD and CD are administered.	parent	*		
	*Social Communication Questionnaire (SCQ, 28*): is a quick screening questionnaire of 40 items for autism spectrum disorders.	parent	*		
	*Kidscreen 27*[29]: 27 item questionnaire that measures quality of life with the dimensions physical well-being, psychological well-being, autonomy & parents, peers & social support and school environment.	child/parent	*	*	*
Intelligence Quotient **	*Shortened version of Wechsler Intelligence Scale for Children**III*[19]*:* subtest Similarities, Block Design, Vocabulary and Information which gives an estimation of the Total IQ	child	*		

T1 = baseline T2 = directly after treatment T3 = follow up after 6 months.

** Intelligence Quotient is only administered if IQ data are not available or when an IQ test has been administered more than two years ago.

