### Sample size

For the randomised controlled trial in the first study with two trial arms, 50 children in each trial arm, an effect size of 0.60 can statistically be demonstrated (P < 0.05, 80% power) for comparison of the primary outcome measures of both interventions. This corresponds with an expected clinically relevant difference of 3 points and a standard deviation of 5 on the subtest Digit span from the WISC-III.

For the second study we developed a risk score for the non-responders of the ‘Paying attention in class’ intervention. We expect that 35% (n = 61) of the 175 included children will show no or insufficient result after the 6 month follow up assessment. With 61 “events”, 4 robust true predictors (15 observations per predictor variable) of non-responders can be identified and used for the risk score of non-responders [30].

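### The named repeated-measures analysis, as usually run, uses complete cases, does not adjust for baseline and gives an omnibus test; a baseline-adjusted mixed model is more efficient and reports the arm difference at each follow-up

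*Protocol article*

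**What the plan says.** The Statistical analysis section of the protocol article names one method for everything: "Multivariate analysis with repeated measures will be conducted, using SPSS Statistics 19 to evaluate training effects on the primary and secondary outcomes". It gives no model terms.

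Three other places bear on how that sentence reads:

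- **Measures and procedures.** Testing "takes place at three consecutive moments: at baseline, directly after treatment and 6 months after treatment". The footnote to Table 1 labels these occasions "T1 = baseline T2 = directly after treatment T3 = follow up after 6 months". Table 1 lists 12 primary measures, each taken at all three.
- **Randomisation.** The clinical research unit "composed a randomisation list, stratified by age", and children are allocated individually.
- **Sample size.** The trial is sized on a difference between arms: with "50 children in each trial arm, an effect size of 0.60 can statistically be demonstrated (P < 0.05, 80% power", tied to an "expected clinically relevant difference of 3 points and a standard deviation of 5 on the subtest Digit span from the WISC-III". No time point is attached to that difference.

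**The concern.** In SPSS, multivariate repeated measures usually means the general linear model procedure, with T1, T2 and T3 as levels of a within-child factor. That has three consequences.

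1. **Complete cases.** A child with any missing value among the variables entered leaves the analysis, including a child seen at T2 but not at T3. This costs precision, and can cause bias if loss is related to outcome.
2. **Baseline as a response.** The group main effect averages in T1, where randomisation rules out a treatment effect. The group-by-time test works on change from baseline, which is less precise than regressing follow-up on baseline.
3. **An omnibus answer.** Over three occasions the group-by-time test has two degrees of freedom. The article wants short- and long-term effects, and it powered a difference between arms. The omnibus test does not itself give that difference, with an interval, at either follow-up.

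At stake are precision, some randomised children, and a directly readable result. The validity of the trial is not at stake.

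**Working it through.** **Inputs from the article.** 50 per arm; difference 3, SD 5; P < 0.05 (taken as two-sided); 80% power; three occasions; 12 primary measures.

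**Inputs assumed, because the article gives none.** Correlation r between occasions of 0.5 or 0.7, equal for all pairs; 5% or 10% of children missing each of T2 and T3, independently; baseline observed for all.

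**Step 1. The plan's own figure.** Effect size 3/5 = 0.60. Normal approximation: n = 2(1.960 + 0.842)²/0.60² = 43.6, so 44 per arm; the t distribution gives 45. At 50 per arm power is 85.1% (normal) or 84.4% (t), and the effect detectable with 80% power is 0.56 to 0.57 SD. The stated 80% is therefore slightly conservative, which neither helps nor hurts this point.

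**Step 2. Baseline as covariate against change from baseline.** In units of the follow-up variance:

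- change score: 2(1 − r)
- ANCOVA: 1 − r²
- ratio, ANCOVA to change: (1 + r)/2

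The detectable effect at 50 per arm is 0.566 times the square root of the variance factor.

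| r | Change factor | ANCOVA factor | Ratio | Detectable, change | Detectable, ANCOVA |
|---|---|---|---|---|---|
| 0.5 | 1.00 | 0.75 | 0.75 | 0.57 | 0.49 |
| 0.7 | 0.60 | 0.51 | 0.85 | 0.44 | 0.40 |

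**Step 3. Complete cases.** 50 × 0.95² = 45.1 and 50 × 0.90² = 40.5, so about 45 or 40 per arm. A mixed model uses every observed follow-up: 50 × 0.95 = 47.5 or 50 × 0.90 = 45 values per arm at each visit. It drops only children who miss both follow-ups, 0.25% or 1% under independence. If the same children miss both visits, this advantage disappears.

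**Step 4. Power at an effect of 0.60.** The two-degree-of-freedom group-by-time test has noncentrality (n/2) × 0.36 × 2/[3(1 − r)], with 2 and 2n − 3 degrees of freedom. This is the same whether the effect is present at both follow-ups or at T2 only. A one-visit comparison has noncentrality (n/2) × 0.36 divided by its variance factor. All columns use the same n.

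| r | n per arm | Group by time, 2 df | Change at one visit, 1 df | ANCOVA at one visit, 1 df |
|---|---|---|---|---|
| 0.5 | 50 | 0.873 | 0.844 | 0.929 |
| 0.5 | 45 | 0.832 | 0.804 | 0.901 |
| 0.5 | 40 | 0.782 | 0.755 | 0.864 |
| 0.7 | 50 | 0.982 | 0.970 | 0.986 |
| 0.7 | 45 | 0.970 | 0.953 | 0.976 |
| 0.7 | 40 | 0.949 | 0.928 | 0.960 |

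**Reading the table.** At r = 0.5 and n = 40 the omnibus test and ANCOVA have the same noncentrality: 20 × 0.36 × 2/1.5 = 9.6 and 20 × 0.36/0.75 = 9.6. The gap between 0.782 and 0.864 is therefore the price of an omnibus rather than a focused test. The effect of baseline handling alone shows in the two one-degree-of-freedom columns: 0.755 against 0.864.

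**The case against.** The strongest reply is that one sentence in a journal article is not a model specification. It does not say that children are dropped, that baseline is a within-child level, that all measures enter one model, or that age is left out. SPSS also fits mixed models and accepts covariates, and such detail commonly sits in a full protocol or analysis plan that is not shown. This stands in part. The consequences follow from the usual reading of the named method, not from explicit text. But the article does name a method, and a better one is available.

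Four stronger readings are tempting, and the documents do not support them.

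- **That the plan ignores the age stratification.** This rests on silence alone. Stable differences between children, including age level, also cancel in a group-by-time test. Adding age is a recommendation.
- **That a third or half of the children would be lost.** With 12 × 3 = 36 cells in one model, 1% missing per cell gives 1 − 0.99³⁶ = 30% lost, and 2% gives 52%. This needs all primary measures in one model and missingness independent by cell. The article states neither, and the child tests are given together at each occasion, so whole-visit loss is more plausible. It is an extreme case.
- **That the detectable effect falls from 0.57 to 0.40 SD.** At r = 0.7 the 0.57 belongs to a comparison of follow-up scores alone, which is not the planned analysis. Against change from baseline the fall is from 0.44 to 0.40.
- **That taking baseline as a response is an error.** It is valid under randomisation, and constrained longitudinal models do the same. Contrasts by visit can also be drawn from a repeated-measures model. The issue is efficiency and direct reporting.

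The remedy has its own price. It assumes data missing at random and needs a covariance choice. It also yields 12 × 2 = 24 primary arm differences, and it does not settle multiplicity.

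**Conclusion.** The point holds as a worthwhile improvement, not as a charge of invalidity. On its usual reading, the named method uses complete cases, does not adjust for baseline and leads with an omnibus test. A baseline-adjusted mixed model uses data the trial already plans to collect, keeps children who miss one follow-up, and estimates the arm difference at each follow-up.

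The size depends on assumed correlations and dropout. At r = 0.5 the gain is material: one quarter less variance than change scores, and with 40 complete cases per arm the omnibus test falls just below 80% power (0.78) while ANCOVA on the same children stays above it (0.86). At r = 0.7 with full data the power difference at an effect of 0.60 is negligible (0.982 against 0.986), and what remains is mainly the kept children and the clearer estimate. Confidence in the reading of the sentence is moderate, because the article does not spell out the model.

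**What to change.** Replace the sentence with a stated model. For each outcome, fit a linear mixed model with:

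- T2 and T3 scores as responses;
- arm, visit, arm by visit, baseline score, baseline by visit, and age (the stratification factor) as fixed effects;
- an unstructured within-child covariance;
- all randomised children with any follow-up, in their allocated arm.

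Report the adjusted arm difference at T2 and at T3 with 95% confidence intervals. State the missing-at-random assumption and how a missing baseline score is handled, since a covariate model otherwise drops that child.

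The cost is analysis wording only: no extra children, visits or measures, and the model can be fitted in SPSS. The price in assumptions is missing at random and the covariance choice. If a joint multivariate test across outcomes is wanted as well, it can be kept as a supplement and labelled so.

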## Discussion

About 3-5% of the children in the Netherlands is diagnosed with AD(H)D [31]. From earlier research we know that AD(H)D has a strong correlation with working memory problems [32,33] which makes it hard for those children to sufficiently benefit from classroom instructions. Treatment with stimulant medications reduces the behaviour symptoms in children with ADHD but the effects on cognitive functioning are less clear. Given the fact that working memory problems and ADHD are both risk factors for academic failure, it is important to develop and investigate interventions that can be implemented at school. Cogmed is already being applied occasionally by school counseling services but the possible transfer effects on academic performance remain unclear. From practice we know that, after thorough diagnostic assessment, both parents and teachers have an urgent need for specific advice on how to cope with and help the child with specific attention and working memory deficits at school or in daily life. Up till now, clinicians provided such advices based on their theoretical and clinical experience, without a standardized method or practical guide to use. With the first study we hope to gain insight in the short and long-term effects of the working memory – and executive function intervention on neuropsychological functioning, academic performance, behaviour in class, behaviour problems and functioning in every day life. This way we can offer health care professionals, teachers and other educational staff members a more standardized and evidenced based guideline in how to approach and treat children with AD(H)D. As mentioned above, Cogmed is a licensed intervention that entails significant costs for healthcare institutions, health care insurance companies and parents. Our intention is to make our experimental ‘Paying attention in class’ available at a low price, which makes it easily accessible for all schools and school counseling services. Healthcare insurance companies require that treatment programs are proven effective, to which we hope to contribute with this study. The second study should give us insight into the effectiveness of both interventions, taking into account individual characteristics, the level of impairment and the costs (stepped-care approach). If both interventions appear to be effective to improve academic performance, they can be implemented in regular and special education schools as an intervention for students who need extra care.

### Strengths and limitations

Our study has several strengths and limitations. Our first study is randomised and controlled, which is the strongest design to establish efficacy, and the sample size is large. Second, Green and colleagues [13] recommended that academic performance, planning, goal attainment and following rules should be assessed as outcome measures in future studies. Our study includes these recommendations by using tests that have been standardized in Dutch samples. Also we assess the quality of life of the children which hasn’t been done in earlier studies. Finally, in both conditions children receive active treatment and children that do not respond sufficiently to the experimental intervention are offered the Cogmed intervention which had already been proven effective. One limitation of this study is that the interventions from the randomised controlled trial differ on certain aspects, primarily on their content and applicability, which could make it difficult to compare the interventions in terms of efficacy. Another limitation, that has been outlined in recent reviews [34,35], is the use of single tasks to assess the generalization effects of working memory training. It is not clear whether the improved performance reflects change to an underlying ability or reflects practice of a task that strongly resembles trained tasks. Therefore we should be cautious when interpreting results on both near and far transfer effects such as attention or academic performance.
